1. ***Methods of randomization and concealed allocation. [Randomization is used to reduce the risk of selection bias. Methods for generating random number sequences include computer software, random number tables, semi-random or pseudo-random methods (such as using dates, birthdays, or even/odd numbers of hospital visits). Please describe the individuals involved in generating random number sequences and the methods they use. Concealed allocation is used in treatment studies to reduce the risk of selection bias. Key steps in concealed allocation include having a designated person determine the allocation sequence, ensuring that this person is not involved in enrolling participants, and securely storing the allocation table. Please provide detailed descriptions of these steps. Central randomization is a robust method of concealed allocation. Describe the individuals and methods involved in determining the allocation sequence]***

(1) In this study, the intervention period for the BMT, which is a behavioural training, lasts for one week. Baseline data, including EEG data, will be collected from all participants. Following this, there will be a one-week training period for the intervention content, after which post-intervention data, including scales, self-reports, and EEG data, will be collected. Follow-up measurements will be conducted at 1 week, 1 month, 3 months, 6 months, and 1 year after the trial's completion. Group allocation will be performed after the completion of baseline data collection.

(2) The primary intervention method employed in this study is the brief mindfulness-based intervention of "STOP" **^[29, 30]^**, with a 7-day ~60-min sessions mindfulness course for the experimental group. Meanwhile, the control group will undergo relaxation training. All recruited participants are from the same school, and due to the lack of blinding execution conditions, achieving double-blind standards may present challenges.

(3) The randomization process for this trial will involve the use of a random sequence generator website (https://www.random.org/). This website will be utilized to ensure the random assignment of participants to either the experimental or control group.

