1. ***Blinding. [Blinding is used in treatment studies and diagnostic trials to reduce the risk of implementation bias and measurement bias. Implementing strict confidentiality measures, such as using placebos or simulating procedures, is an effective blinding method. If blinding is necessary and feasible for your study, describe the methods and procedures for implementing blinding]***

This trial includes group therapy sessions for students from the same school. As a result, participants may already know each other or be unfamiliar with one another, and they may naturally discuss the experimental training they receive. Maintaining blinding for the researchers is challenging as they may be influenced by the experimental content during the trial. Therefore, meeting the requirements of double-blinding in a clinical trial is not feasible in this situation

1. ***Outcome Measures. [Outcome measures are used to evaluate the results of a study and can include primary, secondary, and safety measures, including adverse events and reactions. Please describe the names of the measures, the methods of measurement, and the time points at which they are assessed]***

As listed in **Table 1**, the primary outcomes include subjective reports of smoking craving, changes in EEG indicators, and mindfulness measures (both trait- and state- mindfulness). The secondary outcomes will be daily smoking behaviours (number of cigarettes smoked per day, exhaled carbon monoxide concentration), affect and impulsivity, as well as indicators reflecting correlation between mindfulness and smoking cue-reactivity. Researchers will inquire daily during the intervention period whether participants experience tobacco withdrawal symptoms or any other adverse reactions. Participants are also encouraged to proactively contact the research team if they experience any adverse reactions. Please refer to item 9 for the time points of assessment.

| **Table 1. Evaluated variables** | | | |
| --- | --- | --- | --- |
| **Variables** | **Timepoints** | **Measures** | **Outcome level** |
| **Category 1: smoking related indices** | | | |
| **Nicotine dependence** | -T1, T0, T1-T5 | **Fagerstrőm test for nicotine dependence (FTND)** is a six-item revision of the Fagerstrőm Tolerance Questionnaire **^[31]^**，scored as 0-3 (low), 4-6 (moderate), and 7-10 (high) with the summed score **^[32]^**. | primary |

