| **Craving** | -T1, T0, T1-T5 | **1.Tobacco Craving Questionnaire-Short Form (TCQ-SF**）is short form of 12 optimized projects to assess smoking craving levels，including four factors of emotionality, expectancy, compulsivity, and purposefulness **^[33]^**, with each factor scores from 3 to 21 points, was used in Chinese population**^[34]^**. | primary |
|  |  | **2.Questionnaire on Smoking Urges-Brief（QSU-Brief）**developed by Cox et al., **^[35]^** suitable for multiple measurements in laboratory and clinical use, including 10 items, can be completed in less than 2 minutes. Each item uses a subjective score of 1-7 points to evaluate the current level of craving for tobacco, the Chinese version will be adopted **^[36]^**. |  |
| **VAS for craving** | -T1, T0, T1-T5, during CR task | **Visual analogue scale (VAS)** administered during cue-reactivity experiment to measure the state of craving, responses to each item were rated using a scale that ranged from 0 (not at all) to 10 (the strongest feeling possible). | primary |
| **Number of cigarettes smoked per day** | -T1, T0, T1-T5 | Self-report for number of cigarettes smoked per day. | secondary |
| **Exhaled carbon monoxide (CO)** | T0, T1-T5 | Instantaneous reading device (Bedfont piCO Smokerlyzer) used to identify whether the duration of cigarette cessation meets the requirements. | secondary |
| **Category 2: mindfulness** | | | |
| **Trait-mindfulness** | T0, T1-T5 | **Five Facet Mindfulness Questionnaire（FFMQ）**consisting of 39 items and 5 factors, namely observation, description, acting with awareness, non-reactivity, and non-judging, the Chinese version will be used**^[37]^**. | primary |
| **State-mindfulness** | T0, T1-T5, during CR task | Based on the Toronto Mindfulness Scale (TMS), two items in Chinese version **^[38]^** were used to evaluate the dimensions of curiosity and decentralization. | primary |
| **Category 3: brain function** | | | |
| **Brain function** | T0, T1-T5 | Using a 64-channel EEG system to record in both resting and experimental conditions. | primary |
| **Category 4: Socio-demographic and clinical information** | | | |
| **Self-emotional assessment** | T0, T1 | **Self-assessment manikin (SAM)** used to measure the emotional state during 7-day mindfulness intervention. | others |

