All data will be analyzed upon completion of data collection. The data analysis process will strictly adhere to the principles of the blind method. Analysis of the data will be conducted using R software (https://www.r-project.org/), IBM SPSS Statistics for Windows, V20.0 (SPSS), MATLAB (MathWorks in Natick, Massachusetts, USA), and EEGlab (https://sccn.ucsd.edu/eeglab). Descriptive statistics will be used for demographic, psychological, and behavioural data at baseline. Two-sample t-tests and χ^2^ tests will be performed for continuous and categorical variables between the intervention group and control group. Repeated measures MANOVA will be adopted to examine intervention effects while adjusting for individual factors and pre-intervention variables (e.g., trait mindfulness and smoking indices). Within-group effects will be investigated through serial trend analysis from -T1 to T5. Linear mixed-effects model analysis will include data from all measures at different timepoints to explore factors associated with smoking cue-reactivity for both groups. EEG data will be preprocessed using Matlab software and the EEGLab toolbox. Relative spectrum power for six EEG bands (delta: 1-4Hz, theta: 4-8Hz, alpha: 8-13Hz, low-beta: 13-20Hz, high-beta: 20-30Hz, and low-gamma: 30-48Hz) will be calculated at the single electrode and ROI level. Microstate and phase synchronization analysis will be conducted, and source localization analysis will be used to investigate functional changes in subcortical brain regions. Repeated measures analysis of variance and simple effect analysis will be performed for EEG indices, considering significance in the professional field. Effect size will be measured using Cohen's d or partial eta-squared values **^[46]^**.

1. ***Participant management system.***

(1) **Contact and Guidance:** A contact group consisting of relevant researchers is responsible for providing guidance and addressing any study-related questions for participants throughout the entire study period. This ensures that participants have a clear understanding of the study and can actively cooperate with the research process. Researchers are required to respond promptly and keep records for participants who withdraw, are excluded, lost to follow-up, terminated, or suspended.

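### The repeated-measures ANOVA named for the primary EEG outcome has no baseline covariate, although each participant's EEG is recorded before allocation; adjusting for it would be at least as efficient and costs almost nothing

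*Protocol*

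**What the plan says.** **Status of EEG.** Under Outcome Measures, "the primary outcomes include subjective reports of smoking craving, changes in EEG indicators, and mindfulness measures". The brain-function row of Table 1 has T0 and T1 to T5 as its timepoints, gives the measure as "Using a 64-channel EEG system to record in both resting and experimental conditions", and grades it primary.

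**Timing of T0.** Under Methods of randomization and concealed allocation, "Baseline data, including EEG data, will be collected from all participants", and groups are allocated only once baseline collection is complete. Each EEG index therefore has a pre-randomisation value for the same participant.

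**Analysis.** Three sentences under Statistical analysis methods bear on the point:

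- EEG: "Repeated measures analysis of variance and simple effect analysis will be performed for EEG indices, considering significance in the professional field". No covariate is named, and the role of T0 is not stated.
- Intervention effects: "Repeated measures MANOVA will be adopted to examine intervention effects while adjusting for individual factors and pre-intervention variables (e.g., trait mindfulness and smoking indices"). The sentence does not list the outcomes it covers, and its covariates are examples.
- Mixed model: "Linear mixed-effects model analysis will include data from all measures at different timepoints to explore factors associated with smoking cue-reactivity for both groups". This is exploratory and is not put forward as the treatment comparison.

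**The concern.** The trial aims to show superiority over relaxation training and to identify EEG markers of the effect. The EEG group comparison carries the second aim. The plan collects the covariate likely to be the most useful one, the participant's own T0 value of the same index, but the test named for EEG does not use it as a covariate.

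What the named test does with T0 depends on which part of it is read as the treatment effect:

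- **Group-by-time, with T0 as a time level.** For two occasions this is the t-test on change from T0. It uses the baseline but fixes its coefficient at 1. It therefore over-corrects a chance T0 difference whenever the regression of the later value on T0 has a slope below 1.
- **Simple effect of group at a post-intervention visit.** This ignores T0, so a chance T0 difference between small arms stays in the estimate.
- **T0 as a covariate.** The coefficient is estimated from the data, and the residual variance is never larger than in either of the other two.

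At stake is the precision of a primary outcome, not the validity of the test.

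**Working it through.** **The plan's own figure.** The protocol states no sample size or power for EEG. Its only calculation, under Sample size estimation, is a two-sided paired t-test on QSU-Brief within the experimental group: 4 points, SD 7.65, power 0.80, result 34. With d = 4/7.65 = 0.523 that calculation gives 30.7, so 31. Rounding d to 0.5 gives 33.4, so 34, which is the likely source. This is a separate matter. It is noted because 0.523 and 34 are borrowed below.

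**Inputs**

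| Input | Value | Source |
|---|---|---|
| Standardised group difference | 0.523 | Assumed for EEG; borrowed from QSU-Brief, where it is a within-group quantity |
| Completers per arm | 34 | Stated for the experimental arm; equal control arm assumed |
| Two-sided α | 0.05 | Sample size estimation |
| ρ, T0-T1 correlation of an EEG index | 0.3 to 0.9 | Not in the protocol; shown as a range |

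**Variances** (one post-intervention value, total SD = 1, same SD at both occasions)

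- Group at T1 only: 1
- Change, identical to group-by-time with T0 and T1: 2(1-ρ)
- T0 as covariate: 1-ρ²
- Ratio of covariate to change: (1-ρ²)/[2(1-ρ)] = (1+ρ)/2, which is below 1 for every ρ below 1

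**Power** from the noncentral t, with noncentrality (0.523/√variance) × √(34/2) and 66 degrees of freedom (65 with the covariate). Example at ρ = 0.5:

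- Change: variance 2(1-0.5) = 1.00, noncentrality 0.523 × √17 = 2.16, power 56.5%.
- Covariate: variance 1-0.25 = 0.75, noncentrality 2.16/√0.75 = 2.49, power 68.9%.

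| ρ | Variance ratio, covariate/change | Group-by-time | Group at T1 only | T0 as covariate | Gain over group-by-time | Gain over T1 only |
|---|---|---|---|---|---|---|
| 0.3 | 0.65 | 43.5% | 56.5% | 60.5% | 17 | 4 |
| 0.5 | 0.75 | 56.5% | 56.5% | 68.9% | 12 | 12 |
| 0.7 | 0.85 | 78.3% | 56.5% | 84.5% | 6 | 28 |
| 0.8 | 0.90 | 91.9% | 56.5% | 94.3% | 2 | 38 |
| 0.9 | 0.95 | 99.7% | 56.5% | 99.8% | about 0 | 43 |

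**Sensitivity to arm size.** At ρ = 0.5, 31 per arm gives 52.6% for group-by-time and 64.7% with the covariate. With 45 per arm the figures are 68.9% and 80.8%. The gain is about 12 points in both.

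The table is confined to T0 and T1. With all six occasions, the group-by-time F test has 5 numerator degrees of freedom. Setting it against a single adjusted contrast would mix the effect of the covariate with the effect of testing fewer degrees of freedom.

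**The case against.** A reader might infer that EEG alone is left unadjusted while the behavioural outcomes are corrected for baseline, so that the EEG test throws its baseline away. The protocol does not support this, for four reasons.

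- It never calls the EEG analysis unadjusted. If T0 is a level of time, group-by-time compares change from T0, which fits an outcome worded as changes in EEG indicators. That test uses the baseline and is valid under randomisation.
- The MANOVA sentence does not restrict itself to behavioural measures, offers its covariates only as examples, and does not promise each outcome adjustment for its own baseline. EEG is not expressly excluded from it.
- Simple effects could mean group at a visit, time within group, or stimulus condition in the cue task. Only the first ignores T0, so the last column of the table holds for that reading alone.
- No input to the power figures is an EEG quantity, and at ρ of 0.8 to 0.9 the gain over group-by-time is 2 points or fewer.

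All four stand, and they limit the size and wording of the point. It can also be said that covariate lists belong in a statistical analysis plan that is not shown. That would answer a silent protocol. Here the protocol names the test for a primary outcome, and a later plan that used T0 as a covariate in place of a time level would change that stated method. The exploratory mixed model does not fill the gap.

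**Conclusion.** The point holds as one of efficiency and clarity. The protocol names a repeated-measures ANOVA with simple effects for a primary outcome that has a pre-allocation value, names no covariate, and does not say how T0 enters. Covariate adjustment has variance no larger than change or post-only analysis at any ρ. This ordering follows from the variance formulas and does not depend on the assumed effect size or arm size.

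The size of the gain does depend on assumptions. With 0.523 SD, 34 per arm and two-sided 0.05, the gain over group-by-time is material up to a ρ of about 0.5 or 0.6 (17 to 10 points), modest at 0.7 (6 points) and negligible from 0.8 upwards. The protocol gives no ρ for EEG, and ρ may differ between indices. The named test is not biased or invalid, and the documents do not establish that EEG is singled out for weaker treatment. A change is worth making because it is nearly free and, by the statement under Study design, the trial had not started.

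**What to change.** Under Statistical analysis methods, replace the test named in the EEG sentence with wording such as:

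> *For each EEG index, the between-group effect is estimated from the post-baseline recordings (T1 to T5) in a repeated-measures model with group, visit and group-by-visit, adjusted for the participant's own T0 value of the same index at the same electrode or ROI and in the same recording condition. T0 is not also a level of the visit factor.*

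The same edit should say which outcomes the adjusted MANOVA covers. Which visit carries the main EEG contrast is a separate design choice for the sponsor; the covariate does not require it to be T1 or any other visit.

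The cost is one degree of freedom per index and a simple pre-stated rule for participants without a usable T0 recording, for example imputing the mean T0 value. No additional recordings are needed.

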(3) Access and Time for Public Query of Research Plan: See the publication journal and the China Clinical Trial Registration Center and ResMan Clinical Trial Public Management Platform; 3-5 years.

1. ***Publication Plan. [Provide an estimated timeline and methods for publishing research reports. Specify the number of publications, including interim summary reports if applicable]***

(1) Estimated Time and Method for Research Report Publication: The publication plan will consist of several sections, including the research plan, analysis of panel data using various statistical methods, analysis of psychology-related data, and conclusion.

(2) Estimated Number of Publications: 1 paper (excluding interim summary reports).

1. ***Plan for Sharing Raw Data. [Describe the plan for sharing raw data with the public. Specify the maximum time frame for sharing data, which should not exceed 6 months after the end of the trial. Explain the public platform that will be used for data sharing]***

The original data will be uploaded to the ResMan Clinical Trial Public Management Platform (http://www.medresman.org.cn). The data will be publicly shared no later than 6 months after the end of the trial.

1. ***Treatment and Management of Participants after the Trial Ends. [Describe how participants who have not experienced improvement in their condition at the end of the trial will continue to receive medical care. Explain the measures that will be taken to ensure their ongoing treatment and management]***

In this study, the participants included will be healthy volunteers who will receive guidance from professional teachers in mindfulness training. The goal of this training is to assist participants in effectively managing cravings for smoking by developing skills such as paying attention to and accepting the craving when it arises, and gradually overcoming it. Additionally, this process can enhance the participants' ability to regulate their emotions when confronted with various stressful events in their daily lives.

If, upon completion of the trial, it is determined that the stress level of any participant has reached the clinical threshold, active intervention will be offered by the psychological teachers at the on-campus psychological center. If required, participants will be referred to specialized hospitals for further intervention.

